# Long-term efficacy and impact on rehospitalization of Qishen granules in patients with hypertension and heart failure with reduced ejection fraction: a multicenter, randomized, double-blind, placebo-controlled trial protocol

**DOI:** 10.3389/fcvm.2026.1897966

**Published:** 2026-09-07

**Keywords:** Chinese medicine, clinical protocol, HFREF, hypertension, RCT - randomized controlled trial

## Abstract

**Background:**

Heart failure with reduced ejection fraction (HFrEF) represents a severe manifestation or terminal stage of various cardiac diseases. Long-term hypertension frequently leads to pathological changes such as ventricular remodeling, resulting in HFrEF. Despite continuous advancements in medications targeting hypertension complicated by HFrEF, the five-year survival rate for patients remains below 50%. Chinese Medicine (CM) demonstrates favorable long-term efficacy in managing HFrEF and reducing readmission rates. Focusing on the primary symptoms of HFrEF, we innovatively proposed the syndrome pattern “Toxic Pathogen Syndrome” and developed the effective compound formula Qi Shen Granules (QSG). This trial aims to conduct a prospective clinical study to evaluate the efficacy and safety of QSG in patients with hypertension and HFrEF.

**Methods:**

This is a multicenter, prospective, randomized, double-blind, placebo-controlled clinical trial. A total of 220 eligible participants with hypertension and HFrEF will be recruited and randomized in a 1:1 ratio to receive either QSG or placebo for 12 weeks. All participants received guideline-directed treatment for hypertension and HFrEF throughout the study period. The primary outcome is the improvement rate in plasma NT-proBNP levels from baseline to endpoint and the six-minute walk test. Secondary outcomes include echocardiographic parameters, NYHA functional class, Kansas City Cardiomyopathy Questionnaire (KCCQ), and Heart Failure Toxicity Scale. Safety measures, including liver and kidney function blood tests and adverse events, were used to assess QSG safety. We also conducted follow-up assessments at weeks 26 and 52 to evaluate patient readmission rates and the occurrence of cardiovascular adverse events.

**Discussion:**

The results of this study may establish clinical evidence supporting the therapeutic benefits and safety of QSG in the management of hypertension with HFrEF.

**Clinical Trial Registration:**

http://itmctr.ccebtcm.org.cn/, ITMCTR2025000665.

## Introduction

1

Heart failure with reduced ejection fraction (HFrEF) represents a severe manifestation or terminal stage of various cardiac diseases (1). The global prevalence of heart failure continues to rise. Although drug development has improved clinical outcomes, numerous challenges persist: high hospitalization and mortality rates, with a five-year survival rate still below 50%; intractable issues such as myocardial fibrosis and ventricular remodeling remain unresolved; suitable medications remain unavailable for certain populations, such as those with concomitant renal insufficiency; and long-term medication use carries toxic side effects (2–5).

Chinese Medicine (CM) Demonstrates Significant Efficacy in Treating Heart Failure (6). The enhanced efficacy of modern medicine stems from updated treatment concepts and the discovery of new therapeutic targets, while innovations in understanding pathogenesis are the prerequisite and key to breakthroughs in CM treatment. Although numerous Chinese patent medicines and compound formulas exist for treating heart failure, they predominantly focus on therapeutic approaches such as “Yiqi, Wenyang, Huoxue”, with insufficient innovation in pathogenesis and treatment methodology. Through long-term clinical practice, we observed that patients exhibiting restlessness, dry mouth, thirst, dry stools, rapid pulse, and red tongue with yellow coating frequently experienced acute heart failure episodes or rapid disease progression. Incorporating herbs with detoxifying properties into formulations improved these symptoms and yielded superior treatment outcomes. Therefore, we propose that “toxic pathogens” represent a novel pathogenesis in hypertension complicated by HFrEF. This led to the development of Qishen Granules (QSG), an innovative CM characterized by its detoxifying properties and significant therapeutic efficacy.

Multiple animal and cellular studies indicate that QSG modulates inflammatory pathways to inhibit myocardial injury and improve chronic myocardial ischemia (7, 8). Further clinical studies indicate QSG may serve as a safe adjunctive therapeutic strategy for patients with congestive heart failure (9). However, large-scale clinical research targeting hypertension complicated by HFrEF remains insufficient. Therefore, we designed a multicenter, double-blind, randomized, placebo-controlled trial to investigate the efficacy and safety of QSG in patients with hypertension and HFrEF.

## Methods

2

### Drugs

2.1

QSG are composed of six Chinese herbal ingredients: Astragalus membranaceus 30 g, Aconitum carmichaeli 9 g, Salvia miltiorrhiza 15 g, Lonicera japonica 10 g, Leonurus japonicus 30 g, and Fried Glycyrrhiza uralensis 6 g (Table 1), manufactured by Jiangyin Tianjiang Pharmaceutical Co., Ltd. Granule preparation follows validated procedures. In brief, the herbal medicines are decocted in water, ethanol precipitated, and the extract concentrated under reduced pressure. It is then vacuum-dried and mixed with lactose as an excipient. The placebo contains 5% active ingredients, 93.9% maltodextrin, 1.0% mixed colorants, and 0.1% bittering agent. The placebo is identical to the test agent in color, specifications, packaging, labeling, and content appearance. The herbal materials used for QSG were supplied with manufacturer-issued certificates documenting their botanical origin, geographic source, processing method, pharmacopoeial basis, and material batch number. For safety control, Aconitum carmichaelii was used exclusively in the processed form of Heishunpian rather than as crude Aconitum, and its processing complied with the Chinese Pharmacopoeia 2020. The two blinded investigational products were manufactured by Jiangyin Tianjiang Pharmaceutical Co., Ltd. under batch No. 2411342 and underwent batch-release testing according to the Chinese Pharmacopoeia 2020 and the manufacturer's internal quality specifications. Sixty sachets of each product were sampled for testing. Both products met the predefined requirements for appearance, complete solubility, fill-weight variation and granularity; their moisture contents were 4.0% and 5.0%, respectively. For both products, the total aerobic microbial count and the total yeast and mould count were below 10 cfu/g, and Escherichia coli was not detected. The batch was therefore released as compliant, and the same source-traceability and batch-release requirements will be applied to all investigational products used during the trial.

**Table 1 T1:** Specific ingredients of QSG.

Herbal name	Latin scientific name	Plant part	Weight ratio (g)
Huangqi	*Astragalus membranaeus* (Fisch.)Bge*.*	Roots	30
Fuzi	*Aconitum carmichaelii* Debx.	Roots	9
Danshen	*Sal*via *miltiorrhiza* Bge.	Roots	15
Jinyinhua	*Lonicera japonica* Thunb.	Roots	10
Yimucao	*Leonurus japonicus* Houtt.	Roots	30
Gancao	* Glycyrrhiza uralensis* Fisch*.*	Roots	6

### Design

2.2

This study is a randomized, double-blind, placebo-controlled, parallel-group, multicenter clinical trial supported by the Key Research and Development Program of the Ministry of Science and Technology in China. It was conducted among patients with hypertension complicated by HFrEF. The study was conducted simultaneously at Guang'anmen Hospital of China Academy of Chinese Medical Sciences, Affiliated Hospital of Shandong University of Chinese Medicine, Langfang People's Hospital, Weifang Hospital of Traditional Chinese Medicine, Affiliated Hospital of Xinxiang Medical University, Beijing Changping District Hospital of Traditional Chinese Medicine, Shanxi Provincial Hospital of Traditional Chinese Medicine, China-Japan Friendship Hospital of Jilin University, Linyi Hospital of Traditional Chinese Medicine, Chaoyang Central Hospital, and Yantai Mountain Hospital, enrolling a total of 220 patients. After providing written consent, individuals with hypertension and HFrEF were randomly assigned to receive QSG or placebo for 12 weeks. Standardized treatment followed medication regimens specified in 2017 ACC/AHA/AAPA/ABC/ACPM/AGS/APhA/ASH/ASPC/NMA/PCNA Guideline (10) and the 2022 AHA/ACC/HFSA Heart Failure Management Guidelines (3). Drug types and doses were fixed (unless contraindicated or intolerable). Figure 1 illustrates the study flowchart.

**Figure 1 F1:**
[figure not shown]
Research flowchart.

### Confirmation of case count

2.3

The sample size was calculated based on the expected reduction in serum NT-proBNP levels. Consistent with previous studies demonstrating that a > 30% reduction in NT-proBNP is associated with significantly better prognosis compared to stable or rising levels, efficacy was defined as a > 30% decrease from baseline (11). Based on preliminary research data, the efficacy rates of QSG and placebo after 12 weeks of intervention in chronic heart failure were 50% and 32%, respectively (9). Furthermore, pre-experimental studies demonstrated that QSG significantly improved cardiac function, cardiac structure, and factors related to myocardial hypertrophy in mice with transverse aortic constriction (TAC)-induced heart failure. Therefore, this study projected an efficacy rate of 53% for QSG and 33% for placebo. Given a type-I error rate of *α* = 0.05 and a type-II error rate of *β* = 0.2, and accounting for a 15% dropout rate, the required sample size was calculated using the two-sample comparison of proportions in *PASS* (version 21.0.3) software. This yielded 110 patients per group, totaling 220 cases for both groups.

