### Data analysis and statistical methods

2.15

SPSS 24.0 software will be used to perform statistical analysis on the collected data. All statistical tests will be two-tailed, with a *P*-value ≤ 0.05 indicating statistical significance for the tested difference. Descriptive analysis: Categorical indicators will describe the number and percentage of cases in each category. Quantitative indicators will be described using mean, standard deviation, maximum value, minimum value, median, lower quartile (Q1), and upper quartile (Q3). Comparisons between two groups of general characteristics will be analyzed using appropriate methods based on the type of indicator. For quantitative data, between-group comparisons will employ paired t-tests or Wilcoxon signed-rank tests. For categorical data, chi-square tests or exact probability methods will be used. For ordinal data, Wilcoxon signed-rank tests or the Mann–Whitney U (MWU) test will be applied. Age, atrial fibrillation status and estimated glomerular filtration rate will be recorded at baseline and examined in covariate-adjusted and sensitivity analyses because these factors can materially alter NT-proBNP concentrations. Time to first event will be displayed with Kaplan–Meier curves, compared by the log-rank test, and modeled using Cox regression to estimate hazard ratios (HRs) with 95% confidence intervals. Event counts and recurrent rehospitalizations will be summarized descriptively by group.

The Full Analysis Set (FAS) followed the intention-to-treat principle, including all randomized subjects who received at least one dose of the study drug, with exclusions limited to major protocol violations, no study drug exposure, or complete lack of post-randomization data. The per-protocol set (participants with ≥80% adherence, primary endpoint data and no major protocol violation) will support sensitivity analyses, and the safety set will include all randomized participants who received at least one dose and had a safety assessment. For missing co-primary endpoint data, the prespecified conservative worst-case approach will be used in the primary FAS analysis. Missing data amount, reasons and patterns will be reported by group. Multiple imputation under a missing-at-random assumption will be used as a sensitivity analysis, with additional best/worst-case analyses to evaluate departures from that assumption.

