NYHA cardiac function classification serves as a widely accepted indicator for assessing impaired cardiac function (19, 20). Echocardiography accurately reflects ventricular remodeling and cardiac function status (21), making it one of our secondary outcome measures. Additionally, this study comprehensively evaluated patients’ living conditions, social quality, and physical changes. Therefore, the KCCQ and the Heart Failure Toxic Syndrome Quantification Scale were also considered as secondary outcome measures.

This study involves multiple participating institutions, making quality control one of our primary challenges. We established Standard Operating Procedures (SOP) and provided extensive training to all investigators/physicians prior to patient recruitment. Through initial, supplemental training, and ongoing review, we ensured proper execution of SOP to guarantee data collection quality. Furthermore, we prioritized patient communication to ensure all participants had a thorough understanding of the trial, enabling strict adherence to requirements and attendance at all scheduled appointments.

This study design strictly adheres to the CONSORT guidelines employing a multicenter, randomized, double-blind, placebo-controlled trial design to minimize bias (22). The sample size calculation is scientifically sound, with a follow-up period extending to 52 weeks, enabling thorough assessment of long-term efficacy and safety outcomes. Furthermore, we incorporated readmission rates as a late-stage follow-up indicator, directly linking to health economics metrics, thereby demonstrating strong clinical and practical significance. We anticipate this clinical trial will provide high-level evidence-based medical evidence for the application of traditional Chinese medicine in the field of hypertension-related heart failure.

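### The planning effect was raised from the cited human rates (50% vs 32%) to 53% vs 33% on mouse data alone; at the cited rates, power on the same basis is about 71%, not 80%

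*Protocol article*

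**What the plan says.** Section 2.3 (Confirmation of case count) sizes the trial on the NT-proBNP responder rate, a fall of more than 30% from baseline. It builds the planning rates in three steps.

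- Human data from a cited earlier study: "the efficacy rates of QSG and placebo after 12 weeks of intervention in chronic heart failure were 50% and 32%, respectively".
- Animal data: "pre-experimental studies demonstrated that QSG significantly improved cardiac function, cardiac structure, and factors related to myocardial hypertrophy in mice" with heart failure induced by transverse aortic constriction.
- Conclusion: "Therefore, this study projected an efficacy rate of 53% for QSG and 33% for placebo".

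It then sets the error rates ("Given a type-I error rate of *α* = 0.05 and a type-II error rate of *β* = 0.2"), allows for 15% dropout, and reports 110 patients per group from a two-proportion calculation in PASS. Section 2.15 adds that "All statistical tests will be two-tailed". It also says that missing co-primary data will be handled by a worst-case rule in the primary full-analysis-set (FAS) analysis. The Discussion tells readers: "The sample size calculation is scientifically sound".

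**The concern.** The only human responder rates in the article differ by 18 points. The trial is sized on 20 points, and the sentence that makes the change presents it as following from the mouse work. Cardiac function, structure and hypertrophy markers in mice do not measure how many patients have a fall in NT-proBNP of more than 30%. They may support biological plausibility, but they cannot give a size for a change in that proportion. The change also runs in the direction that lowers the required sample size.

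There is a second, smaller gap. The 80% figure refers to the completers left after 15% dropout, whereas the primary FAS analysis keeps patients with missing values under a worst-case rule. If those patients count as non-responders, both rates shrink, and so does the difference between them.

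At stake is how the design is described. If QSG works as well as the cited study found and no better, the chance of missing the effect among completers is about 28–29%, not 20%. Readers told that the trial has 80% power may then take a non-significant result as stronger evidence against QSG than it is.

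**Working it through.** **Inputs.** From section 2.3: alpha 0.05, beta 0.2, planned rates 0.53 and 0.33, cited rates 0.50 and 0.32, dropout 15%, 110 per arm. From section 2.15: two-sided tests (section 2.3 does not repeat this). Allocation is 1:1. Hence z = 1.960 and 0.842, and (1.960 + 0.842)² = 7.849.

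**Step 1: reproduce the stated sample size.** The unpooled formula is n = 7.849 × [p1(1−p1) + p2(1−p2)] / (p1−p2)².

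- At 53/33: 7.849 × (0.2491 + 0.2211) / 0.04 = 92.3, rounded up to 93. Then 93 / 0.85 = 109.4, rounded up to **110 per arm**, as stated.
- The pooled formula gives 96, which inflates to 113, within 3% of 110.

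**Step 2: the same formula at the cited rates.**

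- At 50/32: 7.849 × (0.2500 + 0.2176) / 0.0324 = 113.3, rounded up to 114. Then 114 / 0.85 = 134.1, rounded up to 135 per arm (270 in total, against 220).
- The pooled formula gives 117, which inflates to 138 per arm.

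**Step 3: power among completers, 93 per arm.**

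Unpooled: power = Φ(|p1−p2| / SE − 1.960), with SE = √{[p1(1−p1) + p2(1−p2)] / n}.

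- 53/33: SE = √(0.4702/93) = 0.0711; 0.20/0.0711 − 1.960 = 0.853; power 80.3%.
- 50/32: SE = √(0.4676/93) = 0.0709; 0.18/0.0709 − 1.960 = 0.579; power 71.9%.

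Pooled: power = Φ([|p1−p2| − 1.960 × √(2p̄(1−p̄)/n)] / SE), where p̄ is the mean of the two rates.

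- 53/33: p̄ = 0.43; (0.20 − 0.1423)/0.0711 = 0.812; power 79.1%.
- 50/32: p̄ = 0.41; (0.18 − 0.1414)/0.0709 = 0.545; power 70.7%.

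Exact enumeration of the pooled chi-square test gives 78.6% and 70.4%.

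**Step 4: missing counted as non-response, 110 per arm.** The assumption is 15% missing in each arm, all scored as failures, so each rate is multiplied by 0.85. The pooled formula is used.

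- 53/33 becomes 45.05% vs 28.05%, a difference of 17.0 points: (0.170 − 0.1273)/0.0639 = 0.669; power 74.8%.
- 50/32 becomes 42.5% vs 27.2%, a difference of 15.3 points: (0.153 − 0.1259)/0.0634 = 0.427; power 66.5%.

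**Step 5: no dropout at all, 110 evaluable per arm.** Power is 85.5% (pooled) or 86.4% (unpooled) at 53/33. At 50/32 it is 77.9% (pooled), 78.8% (unpooled) or 77.5% (exact).

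| Basis | 53% vs 33% | 50% vs 32% |
|---|---|---|
| Completers, 93 per arm (pooled to unpooled) | 79.1–80.3% | 70.7–71.9% |
| Missing = non-responder, 110 per arm (pooled) | 74.8% | 66.5% |
| No dropout, 110 per arm (pooled to unpooled) | 85.5–86.4% | 77.9–78.8% |

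Within each row, the change of rates is worth about 8 points of power.

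**The case against.** The strongest reply is that a planning effect is a judgement. The cited study was in chronic heart failure, while this trial enrols patients with hypertension, LVEF of 40% or less and the toxic-pathogenic syndrome, so its rates need not be the same. Aortic constriction is a pressure-overload model and may have been cited to argue relevance to hypertensive disease. The net change is only 2 points, because the placebo rate was also raised, by 1 point against 3 for QSG. The article does not give the size of the earlier study. Assuming 100 to 500 patients per arm, the standard error of its 18-point difference would be √(0.4676/100) = 6.8 to √(0.4676/500) = 3.1 points, so 20 lies within one standard error of 18.

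Much of this stands. The cited rates are not a benchmark at which 80% power is owed, and 53/33 is not implausible. But a different population and an imprecise estimate widen the uncertainty in both directions. They are reasons to show a range, not to move upward, and the mouse work remains the only reason stated for the higher figures.

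Four stronger readings are tempting and are not supported:

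- That 110 per arm is miscalculated. It reproduces exactly.
- That "a type-II error rate of *β* = 0.2" is false. Beta is defined at the planning alternative, and for completers at 53/33 it holds to within about a point.
- That the trial set aside its own data. The 50% and 32% come from an earlier study in a differently defined population.
- That power drops from 80% to 67%. This sets a completer figure beside one that counts missing values as failures. Compared on one basis, the loss from the change of rates is about 8 points; the remainder comes from the missing-data rule.

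**Conclusion.** The point holds as an unsupported planning assumption with overstated power. The step from 50/32 to 53/33 does not follow from the evidence given for it. Among completers, with 93 per arm, power is about 79–80% at the projected rates and about 71–72% at the cited human rates. With no dropout it still reaches only about 78% at the cited rates, so the shortfall there does not depend on the dropout allowance.

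The figures of about 75% and 67% for the primary FAS analysis are conditional. They assume 15% missing in each arm, with every missing value scored as non-response. The article does not define its worst-case rule in those words, and the FAS leaves out patients with no post-randomization data at all, so the true number scored this way may be smaller. All figures concern the NT-proBNP responder endpoint alone and assume two-sided testing at 0.05.

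**What to change.** In section 2.3:

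- Remove the mouse experiments as support for the higher responder rates. They can stay as background on plausibility. Present 53% vs 33% as an assumption, or cite human data for it if such data exist.
- State power on matched bases. Completers (93 per arm): about 80% at 53/33 and about 71% at 50/32. Missing counted as non-response (110 per arm, 15% missing in each arm, assumption stated): about 75% and about 67%.

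In the Discussion, qualify the statement that "The sample size calculation is scientifically sound" by referring to these figures.

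The cost is one rewritten paragraph and one edited sentence. Enrolment and analysis stay as they are. The only downside is that the stated power looks less favourable.

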### Diagnostic criteria

2.4

#### Hypertension

2.4.1

Hypertension is defined as clinic blood pressure ≥140/90 mmHg in untreated patients, home blood pressure ≥135/85 mmHg, or 24-hour ambulatory blood pressure ≥130/80 mmHg (daytime ≥135/85 mmHg or nighttime ≥120/70 mmHg) (10).

#### Heart failure

2.4.2

Patients must have a history of hypertension and dyspnea. Physical examination should reveal pertinent signs, including pulmonary rales, bilateral lower extremity edema, cardiac murmurs, jugular venous distension, or a laterally displaced/diffuse apical impulse. Electrocardiography may demonstrate abnormalities in heart rate, rhythm, or QRS morphology and duration, such as frequent atrial or ventricular premature beats, atrial fibrillation, or left ventricular hypertrophy. Chest radiography may show findings consistent with pulmonary congestion/edema or cardiomegaly. Echocardiography should confirm the presence of structural and/or functional cardiac abnormalities (3).

#### Toxic-pathogenic syndrome

2.4.3

Diagnostic principles for the Toxic-pathogenic syndrome require a clinically confirmed diagnosis of heart failure with NYHA functional class II–IV. The pattern is established if the patient meets either of the following combinations: a. 1 major criterion + 2 minor criteria + 1 tongue/pulse criterion; OR b. 2 major criteria + 1 minor criterion + 1 tongue/pulse criterion (Table 2).

**Table 2 T2:** Summary of diagnostic criteria for heart failure toxin syndrome.

Dimension	Criteria
Major symptoms	Agitation and restlessness; panting and shortness of breath; chest oppression as if blocked; cold limbs.
Minor symptoms	Orthopnea; lethargy; chest/flank fullness; facial or limb edema; dry mouth and bitter taste; grayish complexion; jugular venous distension; cyanosis of lips/nails; palpitations; fatigue; oliguria; dark-yellow urine; constipation; abnormal inflammatory findings (hs-CRP, IL-6, NLR, or inflammatory changes on chest imaging).
Tongue Appearance	Red tongue with yellow dry coating; dark or reddish-purple tongue; bluish-purple tongue; greasy coating; black coating; or tortuous/cyanotic sublingual veins.
Pulse	Knotted/intermittent, rapid, choppy, or racing pulse.

Assessment will be performed by qualified traditional Chinese medicine physicians at each center using the same scale. Assessors will receive centralized protocol and scoring training before recruitment, with refresher training and monitoring during the trial.

